## Results

3.

All participants’ data required for measurement will be collected and analyzed prior to unblinding. All outcome measures will be evaluated by two researchers, and consensus on the results will be required. If there is no consensus, another researcher will join the evaluation, and serve as arbitrator. Finally, the results will be collected by the principal investigator, and the group allocation information will be unblinded and statistically analyzed. The number of patients who experienced adverse events related to the atorvastatin calcium tablet intervention will be determined by the principal investigator.

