### Randomization and treatment allocation

2.3.

All enrolled patients will be randomly assigned to the atorvastatin treatment group or the placebo control group in a 1:1 ratio (*n* = 90 for each). The randomization sequence will be obtained according to the SPSS software program, and the randomization process will not be stratified. The randomized sequences of group assignments are then hidden in sequentially numbered opaque, closed envelopes. Atorvastatin (Pfizer) and placebo will be stored at the participating hospitals (20–30°C, while avoiding direct lighting), and they will be handled exclusively by the study nurses responsible for drug storage, distribution, and documentation. Placebo tablets are made from dextrin and have the same weight and appearance as atorvastatin. Two types of tablets are made by Shandong ARURA Pharmaceutical Research and Development Co., based on a randomized sequence, and are numbered sequentially. The randomization information and drug type are not publicly available to all investigators, competent physicians, and patients. All patients will be numbered sequentially, and the 8-week dose will be dispensed by the medication nurse in numbered order. At the end of the follow-up visit for the last enrolled patient, the sealed, opaque envelope will be opened by the principal investigator with unblinding (11).

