### Intervention

2.4.

Patients in both groups will undergo standard EDAS procedures. EDAS surgery will be performed by experienced neurosurgeons. The main steps are as follows: (i) in accordance with the blood supply artery, contour the scalp with an incision design, (ii) cut the skin and subcutaneous free out long enough blood supply arteries, (iii) drill a hole on both ends of the bone flap, (iv) form an ellipse milling cutter governor of bone flap, (v) cut an open bar and epidural of about 1-cm width, (vi) maintain epidural blood vessels as far as possible, (vii) sew with fascia artery blood supply on cut epidural, and (viii) return the flap and fix it. The supplying artery remains open.

According to the results of randomization, patients in the experimental group will receive atorvastatin (20 mg/day, once a day, for 8 weeks), and patients in the control group will receive placebo (20 mg/day, once a day, for 8 weeks) from the first day after surgery (11). This dosage was chosen because it had minimal side effects in hyperlipidemia (12, 13), and because a high dose of atorvastatin (80 mg) was shown to increase the risk of bleeding in patients with low body weight and uncontrolled hypertension in a stroke prevention trial that focused on aggressively lowering cholesterol levels (14). Liver and kidney function tests will be performed every 4 weeks during treatment. All drug-related adverse reactions will be communicated to the investigators in a timely manner, and the investigators will decide whether to conduct clinical intervention or withdraw from the study according to the patient-specific situation. All drug-related adverse effects will be documented in detail.

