#### Safety outcomes assessment

2.5.1.

We will evaluate the safety of atorvastatin calcium tablets based on the following events: (1) presence of abnormal liver and kidney function; (2) severe adverse drug reactions, such as death, life-threatening or permanent or severe disability, permanent organ dysfunction, emergency hospitalization or prolonged hospitalization; and (3) new strokes occurring during follow-up after EDAS.

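### Serious events enter the safety outcomes only as adverse drug reactions, relatedness is counted by the person who opens the code with no stated order, and sections 2.3 and 3 time unblinding differently

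*Protocol article*

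**What the plan says.** All references are to the protocol article.

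- **Reporting and documentation (2.4, Intervention).** "All drug-related adverse reactions will be communicated to the investigators in a timely manner", and "All drug-related adverse effects will be documented in detail". The same section schedules laboratory safety tests: "Liver and kidney function tests will be performed every 4 weeks during treatment".
- **Safety outcomes (2.5.1, Safety outcomes assessment).** There are three. The first is "presence of abnormal liver and kidney function". The second is "severe adverse drug reactions, such as death", with life-threatening events, disability, organ dysfunction and emergency or prolonged hospitalisation as further examples. The third is new stroke during follow-up.
- **Who counts related events (3, Results).** "The number of patients who experienced adverse events related to the atorvastatin calcium tablet intervention will be determined by the principal investigator". The sentence gives neither a time nor a blinding status.
- **Unblinding (2.3, Randomization and treatment allocation).** When the last enrolled patient's follow-up visit ends, "the sealed, opaque envelope will be opened by the principal investigator with unblinding".
- **Unblinding (3, Results).** Participants' "data required for measurement will be collected and analyzed prior to unblinding". Two researchers, with a third as arbitrator, must agree on every outcome measure. The principal investigator then collects the results, and the allocation is unblinded and analysed statistically.

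**The concern.** There are three linked weaknesses.

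1. **The gravest events pass through a causality filter.** After cranial surgery in patients with moyamoya disease, whether a death or hospitalisation is due to the drug, the operation or the disease is a matter of judgement. Randomisation makes an any-cause comparison by arm fair without that judgement. Once events are selected by attribution, the comparison is only as sound as the attribution.

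2. **The attribution is not tied to the blind.** One role both opens the envelopes and determines the related-event count. The count is worded as relatedness to atorvastatin, not to study medication in either arm, so the text does not say how an event in a placebo patient is to be classified.

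3. **The unblinding rule is given in two forms.** The primary outcome is a graded reading of the 6-month angiogram that needs consensus. If the code is opened at the last patient's visit, the last readings need not be finished by then.

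At stake are the credibility of the serious-event comparison and, for the last patients enrolled, the masking of the primary reading.

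**Working it through.** The plan gives no safety figure to reproduce. The check therefore sets the sections side by side and then illustrates the size under stated assumptions.

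**Step 1: which safety data depend on attribution**

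| Item | Section | Depends on a causality judgement? |
|---|---|---|
| Abnormal liver or kidney function | 2.5.1, item 1; tested every 4 weeks during treatment (2.4) | No |
| Death, life-threatening event, disability, hospitalisation | 2.5.1, item 2 | Yes, as adverse drug reactions |
| New stroke | 2.5.1, item 3 | No |
| Detailed documentation and reporting to investigators | 2.4 | Worded for drug-related events |
| Principal investigator's count | 3 | Yes, related to atorvastatin |
| Committee review of adverse events | 3.1 | No |

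A death or hospitalisation that is judged unrelated, and is neither a stroke nor a liver or kidney abnormality, meets none of the three outcomes.

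**Step 2: order of events**

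- Section 2.3: last patient's follow-up visit, then envelope opened.
- Section 3: data collected, two readers agree (arbitrator if needed), results collected, then allocation unblinded and analysed.
- The relatedness count is the last sentence of that paragraph in section 3 and has no stated place in either sequence.

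Taken literally, section 2.3 unblinds before the last 6-month readings reach consensus. Section 3 does not.

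**Step 3: what attribution can do to the comparison**

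Inputs: 90 patients per arm (2.3); two-sided 5% level and chi-square test for categorical variables (3.3). Assumptions, not in the documents: the same any-cause event rate *r* in both arms (10%, 20% or 30%), and a share *s* of events judged related in each arm.

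Expected related patients per arm = 90 × *r* × *s*. For example, 90 × 0.20 × 0.60 = 10.8 and 90 × 0.20 × 0.40 = 7.2.

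Test: with X and Y related patients in the two arms and p = (X + Y)/180, z = (|X − Y|/90) / √(p(1 − p) × 2/90). The difference is declared significant if z > 1.96. This is the uncorrected chi-square test. The false-positive rate is the exact binomial probability of that result.

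| Any-cause rate, both arms | Share judged related (atorvastatin v placebo) | Expected related patients | False-positive rate |
|---|---|---|---|
| 10% | 50% v 50% | 4.5 v 4.5 | 0.042 |
| 10% | 60% v 40% | 5.4 v 3.6 | 0.080 |
| 10% | 70% v 30% | 6.3 v 2.7 | 0.208 |
| 20% | 50% v 50% | 9.0 v 9.0 | 0.051 |
| 20% | 60% v 40% | 10.8 v 7.2 | 0.145 |
| 20% | 70% v 30% | 12.6 v 5.4 | 0.441 |
| 30% | 50% v 50% | 13.5 v 13.5 | 0.049 |
| 30% | 60% v 40% | 16.2 v 10.8 | 0.200 |
| 30% | 70% v 30% | 18.9 v 8.1 | 0.625 |

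Equal shares, as expected of blinded attribution, leave the error at about its nominal level. Unequal shares, which need knowledge or a guess of the arm, do not. The table shows attribution tilted against atorvastatin; a tilt the other way could hide a true excess.

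**The case against.** The strongest reply is that the article says less than a quick reading suggests. Four stronger readings are tempting, and the documents do not support them.

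- **That only drug-related events are documented.** The text promises detail for drug-related effects; it does not say that other events go unrecorded. Two of the three safety outcomes carry no relatedness filter, and the monitoring committee in section 3.1 assesses adverse events in general. This reply stands. What remains is the filter on the second safety outcome and on the principal investigator's count.
- **That the count is made after unblinding.** This is an inference from sentence order. The same paragraph puts data collection before unblinding and requires two-reader consensus for all outcome measures, and safety is listed under Outcomes. Reactions are also reported during the trial, while investigators are blinded. This stands too. However, the specific sentence assigns the count to one person, refers to atorvastatin by name, and does not place it before unblinding.
- **That the safety comparison is biased by construction.** Blinded attribution treats both arms alike: it loses information but does not itself create a difference. Bias requires attribution that differs by arm, which the text permits but does not state.
- **That the two unblinding rules flatly contradict each other.** Section 2.3 can be read as meaning once all follow-up is complete, and section 3 then supplies the order. That reading is reasonable, but section 2.3 as written does not require readings or causality judgements to be finished first.

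An article also condenses a fuller protocol, so missing detail on event recording or database lock is not itself a fault. The point rests on what is stated: an outcome defined by relatedness, a count given to the person who breaks the blind, and two unblinding times. The committee is not a clear independent safeguard, because section 3.1 includes principal investigators among its members.

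**Conclusion.** The point holds in a limited form. Serious events enter the second safety outcome only as adverse drug reactions, so some serious events can fall outside every safety outcome. Relatedness is counted by the person who opens the code, with no statement that the judgement comes first. That part of the safety comparison is open to bias; the laboratory and stroke outcomes are not affected by this filter. The unblinding times in sections 2.3 and 3 are not aligned and need one rule.

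The size depends on assumptions that the documents neither give nor exclude. With equal true rates of 10% to 30%, attribution of 60% v 40% would give false-positive rates of 8% to 20%, and 70% v 30% would give 21% to 63%. With equal attribution the rate stays at 4% to 5%. If the events subject to the filter are rarer than 10%, these figures do not apply. Loss of serious events judged unrelated does not depend on these assumptions. The change is worth making because it is cheap and removes the dependence on attribution.

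**What to change.** **Sections 2.4, 2.5.1 and 3.** State that all serious and other adverse events are recorded in both arms regardless of causality and compared by arm. Redefine the second safety outcome as serious adverse events of any cause. Keep relatedness as a secondary classification, worded as relatedness to study medication in either arm, and judged and recorded before unblinding.

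**Sections 2.3 and 3.** Replace the two descriptions with one rule: the code is opened only after all 6-month DSA and MRI readings have reached consensus, causality is recorded and the database is locked. Say in section 3 that comparisons by arm follow that step, so that the analysis mentioned before unblinding is understood as outcome evaluation.

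**Cost.** A wording change and slightly more event recording. No extra staff or visits are needed.

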### Data monitoring agency

3.1.

An independent data safety and monitoring committee consisting of clinicians and principal investigators will be established to oversee the overall conduct of the study. Regular meetings will be held to assess the occurrence of adverse events.

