### Study design

2.1.

This will be a single-center, prospective, randomized, double-blind, placebo-controlled study (Figure 1). A total of 180 patients will be recruited from the Department of Neurosurgery, Chinese PLA General Hospital, and randomly assigned to the atorvastatin treatment or the placebo control group at a ratio of 1:1. The study is planned to run from October 2022 through October 2025.

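### The safety committee is called independent but has principal investigators as members, so they would oversee their own conduct and their own attribution of adverse events

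*Protocol article*

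**What the plan says.** Section 3.1 of the protocol article sets up the oversight body in one sentence: "An independent data safety and monitoring committee consisting of clinicians and principal investigators will be established to oversee the overall conduct of the study". Its only other sentence gives the task: "Regular meetings will be held to assess the occurrence of adverse events". The article names no other body that oversees the conduct of the trial.

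Three other sections give the investigators functions that such a committee would oversee or must not disturb:

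- Section 3 (Results), on attribution of events: "The number of patients who experienced adverse events related to the atorvastatin calcium tablet intervention will be determined by the principal investigator".
- Section 2.4 (Intervention), on individual patients: drug-related reactions are reported to the investigators, who decide case by case whether to intervene clinically or withdraw the patient from the study.
- Section 2.3 (Randomization and treatment allocation), on blinding: "The randomization information and drug type are not publicly available to all investigators, competent physicians, and patients". The blind is lifted only after the last patient's final visit: "At the end of the follow-up visit for the last enrolled patient, the sealed, opaque envelope will be opened by the principal investigator with unblinding".

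Section 2.1 (Study design) fixes the setting: "This will be a single-center, prospective, randomized, double-blind, placebo-controlled study".

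**The concern.** A committee that oversees conduct is independent only if those responsible for that conduct are not on it. Section 3.1 claims independence and, in the same sentence, lists a membership that removes it. This is a positive statement about who sits on the committee. It is not a detail that a short article has left to a charter or a fuller protocol.

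Two things are at stake. First, an ethics committee or a reader will take the word independent as an assurance that someone outside the trial team reviews safety. The safety outcomes in section 2.5.1 include abnormal liver and kidney function, serious drug reactions up to death, and new strokes. Attribution of such events to the drug is a judgement, and here the person who makes it may also help to review it. Second, the membership limits what the committee can look at. Any comparison by arm would put comparative data in front of people whom section 2.3 means to keep blinded.

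**Working it through.** No figure in the article bears on this point, so the check is to set the sections side by side.

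1. **Label against membership.** Section 3.1 says that the committee is independent and that it consists of clinicians and principal investigators. The clinicians may be unconnected with the trial; nothing says that they are trial staff. The conflict lies with the principal investigators.

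2. **Whose principal investigators?** Section 3.1 uses the plural and does not say that they belong to this trial. Sections 2.3 and 3 refer to one principal investigator. As section 2.1 describes a single-centre study, the natural reading is that the committee includes this trial's own lead or leads. That is a reading of the text and is not stated outright.

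3. **Where the functions overlap.**
   - *Attribution:* the principal investigator determines how many patients had drug-related adverse events (section 3), and the committee meets to assess adverse events (section 3.1). The person who attributes the events reviews the attribution.
   - *Conduct:* investigators decide on intervention or withdrawal after a reaction (section 2.4), and the committee oversees overall conduct (section 3.1). Those who make the decisions take part in overseeing them.

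4. **Functions that add little.** The principal investigator also opens the envelopes after the last follow-up visit (section 2.3), and section 3 adds that "the results will be collected by the principal investigator". Both steps come at the end. They concentrate responsibility in one role but create no conflict in safety review while patients are being treated.

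5. **What the committee sees.** Section 3.1 does not say whether adverse events are reviewed by arm, by coded arm or pooled. There are two cases:
   - *By arm:* investigator members see comparative data before the end of follow-up, against the intent of section 2.3. Codes reduce this, but may not remove it if a known drug effect, such as a liver signal, points to the active arm.
   - *Pooled:* the blind stays intact, but the committee is poorly placed to notice an excess of events in one arm.

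Steps 1 to 3 do not depend on step 5. The independence claim fails in either case.

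**The case against.** The strongest reply is that the contradiction is one of wording and that nothing follows from it for the trial's results. The committee's only specific task is to assess adverse events, no interim comparison is planned, and section 2.3 points to blinded review. A principal investigator who attributes events while blinded does not bias the comparison by doing so. Section 2.4 also provides individual monitoring, with liver and kidney tests every 4 weeks. Rules on open and closed sessions belong in a charter that the article need not reproduce.

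Much of this stands. A reader might infer that the committee's meetings will unblind the investigators, or that double-blinding and safety oversight cannot both hold as written. The article does not support that. No section gives the committee data by arm, and a blinded review would leave the allocation sealed, even if it is weaker monitoring. A reader might also infer that knowledge of allocation could reach the grading of collateral vessels. Section 3 assigns outcome evaluation to two researchers with a third as arbitrator; none of them is identified as a committee member or as the principal investigator, and the principal investigator has no stated part in grading.

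The reply does not remove the core. It accepts that section 3.1 claims a property that its own membership list denies, and individual monitoring run by the investigators cannot stand in for independent oversight of them.

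**Conclusion.** The point holds as one of governance and safety oversight. The committee in section 3.1 is not independent as composed, because principal investigators would oversee their own conduct and their own attribution of adverse events. This rests on one assumption, that the principal investigators named there are this trial's own, which is the natural reading for a single-centre study.

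The effect on blinding is conditional. It arises only if the committee reviews adverse events by arm, which the article leaves open.

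No numerical size can be given. The weakness is structural and concerns safety oversight of all 180 planned patients. Nothing in the article shows an effect on the primary outcome or its analysis.

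**What to change.** Reword section 3.1 along these lines: *The data safety and monitoring committee consists of clinicians who take no part in the conduct, outcome reading or analysis of the trial. Principal investigators are not members and receive at most safety data pooled over the two arms.* It would help to add a phrase saying whether the committee's own review is by arm or pooled, but the point does not depend on that; session rules and table formats can stay in a charter.

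If the membership cannot be changed, drop the word independent, so that the article does not claim an assurance that the trial lacks. This corrects the description but leaves the oversight as weak as before, so it is the second choice.

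The cost is small. Uninvolved clinicians stay on the committee, and the sample size, treatment, visits and analysis are untouched. The downside is that the investigators lose direct access to committee discussions.

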### Sample size estimation

3.2.

Using the normal approximation method and Pearson Chi-square test sample size calculation formula for the rate comparison between the two groups, test level *α* = 0.05 and test efficiency 1−β = 0.80 were set. According to the preliminary experimental results of this project, the probability of formation postoperative collateral networks (grade A or grade B) in patients with MMD treated with atorvastatin was 79.1%. The incidence in development of postoperative collateral vessels (grade A or B) in patients with MMD who were not treated with atorvastatin was 58.2%. Assuming that the coefficient of sample size relationship between the experimental group and the control group, K, is equal to 1, the minimum sample size for the two groups was calculated as *n* = 77, with the estimated loss to follow-up rate and rejection rate at 10%. The final total minimum sample was *n* = 154/0.9 = 172. We ultimately began with 180 cases.

### Statistical analysis

3.3.

All data will be analyzed by intention-to-treat and per-protocol. Categorical variables will be analyzed by chi-square test and continuous variables will be compared by independent *t*-tests or ANOVA. A U-test will be performed for variables that do not follow a normal distribution. Univariate analysis will be used to assess age, sex, initial symptoms at diagnosis, collateral grade, posterior circulation involvement, and use of atorvastatin. Variables significantly associated will be selected and analyzed by multiple linear regression. A value of *p* < 0.05 will be considered statistically significant. SPSS 26.0 software will be used for statistical analysis of all data.

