#### The primary outcomes

2.5.2.

The main outcome will be the formation of collateral blood vessels in patients 6 months after EDAS and it will be measured by DSA. Additionally, we will compare whether there are statistical differences between the experimental and the control group and analyze whether there is a correlation between the effect of vascular reconstruction and the application of atorvastatin.

The standard evaluation of the formation of collateral vessels relies on the Matsushima grading: grade A, the superficial temporal artery compensates to the intracranial mass, covering more than 2/3 of the blood supply area of the middle cerebral artery; grade B, the superficial temporal artery compensates to the intracranial middle one in equal amount, covering 1/3–2/3 of the blood supply area of the middle cerebral artery; grade C, there is no communication between the superficial temporal artery and the intracranial one, no growth to the intracranial artery, or a small amount of compensation from the superficial temporal artery to the intracranial one, covering 0–1/3 of the blood supply area of the middle cerebral artery (15).

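### The adjusted analysis admits atorvastatin only if it is already significant on its own, and uses a linear model that does not suit the graded primary outcome

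*Protocol article*

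**What the plan says.** Section 2.5.2 defines the primary outcome as collateral formation on DSA six months after surgery: "The standard evaluation of the formation of collateral vessels relies on the Matsushima grading", which has three ordered grades, A, B and C. The same section adds an aim of relating the result of the reconstruction to the use of atorvastatin. Section 3.2 sizes the trial with the Pearson chi-square formula on the proportion with "postoperative collateral networks (grade A or grade B").

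Section 3.3 then gives two kinds of analysis.

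- **Group comparison.** "All data will be analyzed by intention-to-treat and per-protocol". For the tests: "Categorical variables will be analyzed by chi-square test and continuous variables will be compared by independent" t-tests or ANOVA.
- **Regression.** "Univariate analysis will be used to assess age, sex, initial symptoms at diagnosis, collateral grade, posterior circulation involvement, and use of atorvastatin". The next sentence reads: "Variables significantly associated will be selected and analyzed by multiple linear regression".

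The dependent variable of the regression is not named, and no other multivariable model appears in the article.

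**The concern.** Three features of the regression rule cause trouble.

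1. **The randomised treatment is screened.** The candidate list ends with "collateral grade, posterior circulation involvement, and use of atorvastatin". Treatment therefore enters the model only after a significant univariate result. A trial with a non-significant crude effect yields no adjusted estimate, and every adjusted estimate that is reported has been selected for significance. This holds whatever the dependent variable is.
2. **The model type.** If the dependent variable is the Matsushima grade, linear regression either treats A, B and C as equally spaced numbers or treats a yes/no outcome as continuous.
3. **Collateral grade as a predictor.** If this means the six-month grade, it is either the outcome predicting itself or, in a model for perfusion or mRS, a variable measured after randomisation that can absorb part of the treatment effect.

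The adjusted result matters more than usual here. Randomisation is unstratified (section 2.3), and the Discussion itself warns that baseline and Suzuki-stage differences may bias the results. A prespecified adjusted estimate is the natural answer to that worry, and the present rule makes it conditional on significance.

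**Working it through.** **Inputs from the article.** Grade A or B: p1 = 0.791 with atorvastatin, p2 = 0.582 without (section 3.2). α = 0.05, power 0.80 and 10% loss (section 3.2). 90 randomised per arm (section 2.3), so 90 × 0.9 = 81 evaluable per arm. Sidedness is not stated; two-sided reproduces the article's figure.

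**Step 1: reproduce the sample size.** With p̄ = (0.791 + 0.582)/2 = 0.6865 and d = 0.209,

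n = [1.960·√(2·p̄·(1−p̄)) + 0.842·√(p1(1−p1) + p2(1−p2))]² / d²

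= [1.960 × 0.6561 + 0.842 × 0.6392]² / 0.04368 = (1.286 + 0.538)² / 0.04368 ≈ 76.2, rounded up to **77 per group**.

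Then 154/0.9 = 171.1, rounded up to **172**. Both agree with section 3.2. The sample size thus rests on the unadjusted two-proportion test, which does not pass through the screen.

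**Step 2: chance that treatment passes the screen.** With the primary outcome as A/B versus C, passing is the same event as a significant crude test. At 81 per arm:

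z = (0.209 × √81 − 1.286)/0.6392 = (1.881 − 1.286)/0.6392 = 0.931, so the probability is 82.4%.

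**Step 3: size of the difference among trials that pass.** The smallest difference that reaches significance at 81 per arm is about 1.286/√81 = 0.143, or 14.3 points. Smaller observed differences are filtered out, so the average of those that remain lies above the truth. A simulation of 400,000 trials per row (two independent binomials, pooled z-test, |z| > 1.96) gives:

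| Atorvastatin v control | Per arm | Passes | No adjusted effect | True difference | Mean difference if passed |
|---|---|---|---|---|---|
| 79.1% v 58.2% (article) | 81 | 82.9% | 17.1% | 20.9 | 23.1 |
| 79.1% v 58.2% (article) | 90 | 86.4% | 13.6% | 20.9 | 22.6 |
| 70% v 58.2% (assumed) | 81 | 34.9% | 65.1% | 11.8 | 19.7 |
| 65% v 58.2% (assumed) | 81 | 14.1% | 85.9% | 6.8 | 18.4 |

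Differences are in percentage points. At the article's rates and 81 per arm the inflation is 23.1/20.9 = 1.1. At the assumed 70% it is 19.7/11.8 = 1.7.

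The simulated quantity is the crude risk difference, used as a stand-in for the adjusted effect. The article gives no covariate effects from which an adjusted estimate could be simulated.

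**Step 4: model and predictor list.** No arithmetic applies, so the sections are compared.

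- Section 2.5.2 gives an ordered three-level grade, and section 3.2 reduces it to A/B versus C. Section 3.3 offers only a linear model. The aim in section 2.5.2 of relating the reconstruction result to atorvastatin suggests the grade as the dependent variable, but section 3.3 does not say so.
- The only collateral grade the article defines is the Matsushima grade, which describes supply from the superficial temporal artery and is the six-month outcome. The candidate list does not say whether its collateral grade is that one or a preoperative one.

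**The case against.** The strongest reply is that the treatment comparison does not depend on the regression at all. Section 3.3 assigns categorical variables to the chi-square test, by intention-to-treat and per-protocol. Section 3.2 sizes the trial for that test. The test is unadjusted, valid in a randomised trial, and reported whether or not atorvastatin passes the screen. This stands. A reader might infer that the primary result or its type I error is compromised, and the documents do not support that.

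Second, the dependent variable is unnamed. Section 2.5.3 has continuous perfusion measures for which a linear model would be suitable, and even for a yes/no outcome a linear model's treatment coefficient estimates a risk difference. This stands in part: that the regression is fitted to the grade is a reasonable inference, not a stated fact. The unsuitable-model point is therefore conditional.

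Third, collateral grade stands in the list beside patient characteristics such as age and initial symptoms, so a preoperative meaning is possible. That is fair, and it makes the circularity conditional too.

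Fourth, a 1.7-fold inflation is a tempting headline, but it rests on a 70% rate that appears nowhere in the article. At the documented rates it is about 1.1-fold.

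Last, this is a condensed article, and covariate details may sit in an analysis plan that is not shown. That would excuse silence. It does not excuse the screening rule, which the article states outright and applies to the randomised treatment by name.

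**Conclusion.** The planned adjusted analysis is wrong as written, and it is a supportive analysis. The firm part is the screen: treatment must be univariately significant before it is modelled, so an adjusted effect is available only after a significant crude one. At the article's rates with 81 evaluable per arm, it would be missing in about 17% of trials, and the crude difference among trials that pass would average 23.1 against a true 20.9 points. If the true rates were 70% v 58.2%, which is an assumption, the figures would be about 65% missing and 19.7 against 11.8 points. They assume that the screen is applied to A/B versus C at two-sided 0.05.

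Two further faults are conditional: an unsuitable model if the Matsushima grade is the dependent variable, and a circular or post-randomisation predictor if collateral grade means the six-month grade. That selecting covariates by p-value would also distort the final model's standard errors is a fair general worry, but no figure for it can be derived from the article and the conclusion does not need it.

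**What to change.** Replace the screening and regression sentences in section 3.3 with text along these lines:

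> The adjusted analysis of the primary outcome is a logistic regression of grade A/B versus C at six months (or an ordinal regression of A/B/C). Treatment is always in the model. Baseline covariates are fixed before unblinding: age, sex, initial symptoms and posterior circulation involvement. No variable is selected by univariate significance.

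The covariates shown are those the article already lists. Suzuki stage is an option, since the Discussion names it as a source of possible imbalance. Remove use of atorvastatin from any screened list, and restrict collateral grade to a preoperative grade or delete it. If a linear model is meant for the perfusion measures, name that outcome and keep treatment in the model there as well.

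The cost is a wording change before unblinding. SPSS 26.0, the stated software, fits logistic and ordinal models. No new data are needed if the listed covariates are used, and the sample size stays at 77 per group and 172 in total.
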